## Abstract

**Background:**

Physical inactivity is prevalent, leading to a high burden of disease and large healthcare costs. Thus, there is a need for affordable, effective and scalable interventions. However, interventions that are affordable and scalable are beset with modest effects and engagement. Interventions that integrate machine learning with real-time data to offer unprecedented levels of personalisation and customisation might offer solutions. The aim of this study is to conduct a randomised controlled trial to evaluate the effectiveness of a machine learning and app-based digital assistant to increase physical activity.

**Methods:**

One hundred and ninety-eight participants will be recruited through Facebook advertisements and randomly allocated to an intervention or control group. Intervention participants will gain access to an app-based physical activity digital assistant that can learn and adapt in real-time to achieve high levels of personalisation and user engagement by virtue of applying a range of machine learning techniques (i.e. reinforcement learning, natural language processing and large language models). The digital assistant will interact with participants in 3 main ways: (1) educational conversations about physical activity; (2) just-in-time personalised in-app notifications (‘nudges’), cues to action encouraging physical activity and (3) chat-based questions and answers about physical activity. Additionally, the app includes adaptive goal setting and an action planning tool. The control group will gain access to the intervention after the last assessment. Outcomes will be measured at baseline, 3 and 6 months. The primary outcome is device-measured (Axivity AX3) moderate-to-vigorous physical activity. Secondary outcomes include app engagement and retention, quality of life, depression, anxiety, stress, sitting time, sleep, workplace productivity, absenteeism, presenteeism and habit strength.

**Discussion:**

The trial presents a unique opportunity to study the effectiveness of a new generation of digital interventions that use advanced machine learning methods to improve physical activity behaviour. By addressing the limitations of existing conversational agents, we aim to pave the way for more effective and adaptable interventions.

**Trial registration:**

Australian New Zealand Clinical Trial Registry ACTRN12624000255583p. Registered on 14 March 2024. https://www.anzctr.org.au/Trial/Registration/TrialReview.aspx?id=387332.

**Supplementary Information:**

The online version contains supplementary material available at 10.1186/s13063-025-08926-3.

## Introduction

There is a wealth of evidence regarding the benefits of regular physical activity [1]. Physical activity guidelines recommend a minimum of 150 min of moderate-to-vigorous physical activity per week to prevent the development of cardiovascular disease, diabetes, obesity, cancer and depression [2, 3]. Yet, more than a third of the world’s population does not meet these guidelines [4], causing 9.4% of the total burden of disease and estimated to cost INT$520 billion between 2020 and 2030 through healthcare costs and lost productivity [5, 6]. Therefore, there is an important need to develop and evaluate interventions that can increase physical activity at a population level and at an affordable cost.

Unfortunately, increasing physical activity at a population level has been difficult to achieve. While intensive face-to-face counselling by health professionals is effective, it cannot be implemented at scale due to limited feasibility and high costs [7]. Alternative methods to increasing activity levels at scale (e.g. phone, print, websites, apps) have shown promise, but effect sizes tend to be modest [8–10]. As such, the challenge to develop effective, affordable and scalable physical activity interventions remains. In this context, the application of machine learning and artificial intelligence to increase activity levels is increasingly gaining interests by behavioural scientists.

While the concepts of machine learning and artificial intelligence were first established in the 1950 s [11], it has taken more than 60 years for their broad application and implementation in today’s society, due to a lack of computer processing power and speed [12]. Though, right now, we are experiencing nothing short of a revolution in terms of the rapid proliferation and adoption of very powerful machine learning applications (e.g. it took less than 2 months for ChatGTP’s large language model to reach a 100 million users).

Previously, computer-based expert systems have applied basic If–Then decision-rules to provide personal physical activity advice (so-called computer-tailored interventions) [13]. Though these interventions demonstrated superior effectiveness compared to generic or targeted interventions [14], they are not optimally suited to handle the complex and dynamic nature of behaviour change and are not able to provide the right support at the right time (i.e. just-in-time adaptive interventions) [15]. Yet, physical activity interventions that apply machine learning algorithms might be able to overcome the limitations of the previous generation of computer-based interventions.

Some have already examined the use of machine learning to increase physical activity levels [16–18], and while the outcomes of these studies have been promising, it is important to point out that the methodological rigour in those studies was low and that the true application of machine learning has been limited. Most of these studies have examined chatbots that have applied off the shelf natural language processing (NLP) but have not implemented machine learning techniques that involved high levels of personalisation or the use of real-time data from activity sensors to deliver just-in-time messages [16–18].

Therefore, based on our initial work in this area [19, 20], we published an innovative concept of a sophisticated machine learning-based digital assistant, able to provide highly personalised physical activity advice, delivered just-in-time based on real-time data [21]. After completing focus group research [22], co-creation workshops, software development and extensive beta-resting, we have now developed a digital assistant that is able to dynamically and proactively nudge users into being more physically active. Our intervention applies machine learning techniques rarely applied to increase physical activity to date (i.e. reinforcement learning). In addition, the intervention also uses NLP, along with an integrated large language model (i.e. Google’s Gemini) that can formulate coherent and relevant answers to any physical activity-related questions participants may have. Now that the development phase has been completed, we are ready to evaluate the effectiveness of this new intervention. For this evaluation, we will focus on workplace-based employees, as workplaces offer a captive audience to implement interventions to large populations for potential future translation efforts [23]. Moreover, workplace interventions can achieve outcomes that go beyond health benefits, such as improved productivity, workplace morale, reputation and lower absenteeism [24]. Therefore, the aim of this study is to conduct a randomised controlled trial to examine the effectiveness of a machine learning and app-based digital assistant to increase physical activity in office-based employees. We hypothesise that participants receiving the intervention will significantly increase their moderate to vigorous physical activity at 3- and 6-month follow-ups compared to participants allocated to a no intervention control group.

## Methods

### Trial design

The MoveMentor trial is a parallel group, two-arm, superiority trial with a 1:1 allocation ratio to investigate the effectiveness of an app-based digital assistant to increase physical activity compared to a no intervention control group. Given the novelty of the intervention, we first need to establish the effectiveness of the intervention against a true control group, prior to comparing it to alternative interventions. The control group will be offered access to the intervention after the final assessment has been completed. The study setting is ‘home-based’, as there will be no face-to-face contact with participants, and all communication will occur via e-mail or phone. Primary and secondary outcomes will be assessed at baseline, 3 months and 6 months. The study has received ethics approval from the Human Research Ethics Committee (HREC) of the Central Queensland University (0000024786) and complies with the Helsinki Declaration. While not anticipated, any adverse events will be reported immediately to the HREC and managed according to their instructions and reported in publications resulting from this study. Likewise, ethical approval will be sought prior to any protocol amendments should they be needed. The Central Queensland University is the sponsor for this trial. There are no plans to use participants’ data in any other studies. This study protocol has been prepared in accordance with SPIRIT guidelines (see Additional file 1 and Table 1) and study outcomes will be reported according to CONSORT guidelines [25, 26].

**Table 1 Tab1:**
[figure not shown]
SPIRIT figure

### Participants

One hundred and ninety-eight participants will be recruited through Facebook advertisements. As response rates to Facebook advertisements are lower in men [27], more funds will be spent on advertisements targeting men, as to obtain a reasonably balanced sample. Recruitment rates will be closely tracked throughout the recruitment phase to determine how much should be spent on advertisements for each gender. All advertisements will direct interested individuals to a Qualtrics survey for screening. After potential participants have completed the screening questionnaire and are deemed eligible, they will be provided with a detailed study information sheet. If those deemed eligible are still interested in participating, they will be asked to provide contact details and informed consent. Those deemed ineligible will be informed of why, but they will not be able to continue.

Eligible participants will be:Over 18 years of ageLive anywhere in AustraliaSpeak and read the English languageEngaged in full-time office-based employmentHave a smartphone (i.e. Apple or Android) with internet accessBe physically inactive. Participants will be asked: ‘*How many days per week do you engage in at least 30 min of activity of a moderate intensity or physical activity higher? For example, brisk walking, swimming, tennis, *etc.*?*’ Anyone reporting more than 2 days per week will be excluded.Have no impairments limiting an increase in physical activityDid not participate in any physical activity programs in the past 12 monthsNot own or have used a physical activity tracker for at least 12 monthsNot be pregnantHave a body mass index over 17.5

### Procedure

When contact details of eligible people are received through the Qualtrics survey, a project officer will make contact by phone to verify the information provided, make sure they are aware of and understand all study requirements and that they still agree to participate. Subsequently, they will be e-mailed a link to access to an online baseline survey (administered via Qualtrics). Participants will also be sent an accelerometer-based activity monitor using registered mail, as well as instructions on how to use the device, a 7-day monitoring log and a pre-paid return post bag. They will be asked to wear the activity monitor on the non-dominant wrist for 7 consecutive days and nights from the day of receipt. When the accelerometer is returned to the laboratory, it will be checked for valid wear time. Potential participants providing less than four valid monitoring days (≥ 10 h of wear time) will be excluded from the study. The same measurement procedures (online survey and 7-day accelerometer) will be repeated at 3 and 6 months (though participants with incomplete data will not be excluded at this stage). Participants will be rewarded with a $50 AUD shopping voucher for each completed assessment. Participants can withdraw from the study without any consequence at any stage. Whenever needed, reminder e-mails and phone calls will be used to encourage participants to complete assessments.

In accordance with the approved study data management plan (DMP_2790), data from all sources will be securely stored for a minimum of 10 years on a university server dedicated to research data and regularly backed up. Only study investigators named on this publication will have access to the final trial dataset. Given the small scale of this study, no data monitoring committee will be established beyond the involvement of the study investigators named on this publication. Participants’ identity will be protected at all times; only de-identified and aggregated data will be disseminated in publications and reports. A plain English statement summarising trial outcomes will be shared with participants that indicated an interest. Publications resulting from this study will abide by ICMJE authorship guidelines and not involve professional writers.

When the initial activity monitoring period and baseline survey have been completed, participants will be randomised into one of two groups using a randomly generated sequence created by CV within Microsoft Excel (version 16.89.1, Microsoft Corporation, Redmond, WA). The column containing the randomised sequence will be concealed in the spreadsheet and will only be unmasked row-by-row by the study manager (DH) after a new participant has been added to the spreadsheet. After randomisation, intervention group participants will be sent a Fitbit Inspire 2 activity tracker (Fitbit Inc, San Francisco, CA) as part of the intervention. They will be asked to download the Fitbit app onto their smartphone, connect their Fitbit tracker with this app and wear the Fitbit for at least 7 days. The Fitbit is worn on a participant’s preferred wrist, with the dominant or non-dominant wrist preference recorded in the Fitbit app on setup. After this, they will be asked to download the digital assistant smartphone app (i.e. *MoveMentor*) onto their smartphone and grant permission for *MoveMentor* to access their Fitbit data. Once everything is set up, intervention group participants will be asked to wear their Fitbit as much as possible and actively engage with the *MoveMentor* app during the 6-month intervention period. Intervention participants’ use of *MoveMentor* will be monitored for the entire 6-month study duration. Intervention participants who do not download or use *MoveMentor* will be encouraged to download and/or use to use the app via e-mail. Given the behavioural nature of the study, aspects of concomitant care are not applicable in this study. At the end of the study, intervention group participants will be able to keep the Fitbit activity tracker and access to the MoveMentor app will continue to be available via the Apple App and Google Play stores for all study participants. The flowchart in Fig. 1 shows an overview of the study procedures.

**Fig. 1 Fig1:**
[figure not shown]
Flowchart

### Intervention

A detailed description of the intervention concept has been published elsewhere [21]; this includes in-depth information on how machine learning aspects have been applied. Briefly, the intervention consists of a stand-alone smartphone app (for both Apple and Android operating systems) named *MoveMentor* (see Fig. 2). The app works in conjunction with physical activity trackers (e.g. Fitbit). The main feature of the app is the physical activity digital assistant (i.e. chatbot or conversational agent). While the name of the digital assistant in the app stores is *MoveMentor*, users can change the name inside the app and select one of three main characters (i.e. *MoveMentor* (default), *MoveMate* or *MyPT*) or choose their own name and image for the digital assistant.

**Fig. 2 Fig2:**
[figure not shown]
Image of the MoveMentor app homepage

The digital assistant interacts with participants in 3 main ways: (1) educational conversations; (2) nudges (via smartphone push notifications) and (3) chat-based questions and answers (Q&A). The conversations provide participants with educational content in relation to physical activity delivered through interactive ‘conversations’ or ‘chats’. The aim of the conversations is to encourage participants to become more physically active and meet the national physical activity guidelines (i.e. 150 to 300 min of moderate-to-vigorous intensity physical activity), as well as to support them in overcoming any difficulties in becoming more active [28]. The conversations are supported by Google’s Dialogue Flow and use natural language processing to enable a more natural flow for the conversation. Example conversation topics include ‘*Developing a lasting activity habit*’, ‘*What stops you from being active?*’, ‘*Make the most of your surroundings*’, ‘*Being active with others*’ and ‘*Building confidence for being active*’. During the conversations, the *MoveMentor* will ask participants physical activity questions and participants will be provided with personalised advice, depending on the answers they provide. Additional resources are provided at the end of each conversation for further reading, watching or listening. The conversations are designed to last no longer than 5 or 10 min. A list of conversations is available for participants on the homepage of the app; however, participants will also receive ‘nudges’ (i.e. notifications) to engage in these conversations. Participants will be able to go through a conversation more than once if they want to do so. The conversations have been informed by the Self-Determination and Social Cognitive Theories [29, 30].

Based on the ‘Nudge’ and ‘COM-B’ theories (Capability-Opportunity-Motivation and Behaviour), participants will also be nudged into action [31, 32]. The nudges (delivered as a smartphone push notification) should be thought of as a Just-In-Time Adaptive Intervention (JITAI), which uses real-time data to dynamically address user needs by providing the right cue to action at the right time to assist with long-term habit formation [15]. The timing and content of the nudges are determined by machine learning algorithms that learn what works for whom under what circumstances through trial and error. The machine learning algorithm is trained to make the nudges more personally relevant over time and will use real-time feedback from activity trackers to learn what nudges work and do not work (i.e. an increase in physical activity following nudges or not). The nudges that work will be reinforced, and those that do not will be phased out. More specifically, a ‘contextual bandit’ approach is applied to deliver the right nudges at the right time; this is a type of reinforcement learning [33, 34]. Contextual data will be derived from participants’ app preferences and settings (derived using an onboarding survey), participant interactions with the app and digital assistant, physical activity data from the activity trackers, nudge ratings (i.e. like or dislike) and weather data (to determine whether indoor or outdoor activity is recommended based on the participants’ location at that specific time). An extensive library of nudges has been developed to send to users through push notifications. The library consists of a range of nudge categories from which nudges are selected in a random pattern. However, a nudge that has been used before will not be used again unless all other nudges within a category have been used as well. Examples of nudge categories are ‘daily morning check-in’, ‘weekly action plan review’, ‘activity suggestion’ (e.g. inspirational, based on known participant characteristics, based on weather), ‘motivational’ (i.e. to encourage meeting their daily activity goal), ‘educational’ (i.e. physical activity facts, tips and tricks), ‘streaks’ (i.e. achieving daily goals repeatedly), ‘milestones’ (e.g. recording over a million steps) and more. The reinforcement learning algorithms have been trained with the help of 300 beta-testers over a 6-month period to improve their performance.

Finally, participants can engage with the digital assistant by asking it physical activity-related questions. Answers to questions that have not been pre-programmed (e.g. I have a muscle pain in my calf, how can I still be active?) are being delivered by Gemini (Alphabet Inc, Mountain View, CA), Google’s machine learning and natural language generation model (it is a large language model comparable to ChatGPT). To generate the best answer, additional contextual information will be sent to Gemini. This will include previous conversations, the user’s nominated username, recent physical activity, local weather and other information provided during the usage of the app. The answer will be generated by the Gemini algorithms.

Beyond interactions with the digital assistant and personalisation features, the *MoveMentor* app includes additional features, of which adaptive goal setting and action planning are the most important. Every morning, participants receive a daily activity goal (expressed as steps or activity minutes, as per participant preference). This goal is based on whether they met their activity goal during the previous day, as well as the average physical activity conducted in the last 4 weeks. The goal is designed to slowly increase over time, aligned with how well participants are performing, until it reaches a participant’s ‘long-term activity’ goal (defined as part of the action planning process), at which point the goal stops increasing. If participants are consistently not meeting their daily activity goal, then the goal will gradually decrease, to better align with the participant’s activity journey.

Participants are encouraged to engage in an action planning process [35]. This conversation is designed to help participants formulate a weekly action plan. If participants are to achieve their long-term goal, they need concrete short-term action. As such, the action plan helps participants define what physical activities they will engage in, where they will do them, how many times per week, what days of the week, what time of day, how long activity sessions will last and identify any people they may be active together with. To be effective, action plans need to be updated regularly and the digital assistant will send out a weekly reminder to review participants’ action plans.

Control group participants will not receive access to the intervention until after the 6-month waiting period. They will not receive a Fitbit activity monitor.

### Measures

#### Primary outcome

Device-measured moderate-to-vigorous physical activity: Participants will be asked to wear an Axivity AX3 tri-axial accelerometer (https://axivity.com/product/ax3) on their non-dominant wrist for 7 consecutive days during waking and sleeping hours, except when swimming, bathing or participating in contact sports. Participants will also be asked to complete an activity monitor log detailing times the monitor was removed, time they went to bed and wake up time. The Axivity AX3 has demonstrated good concurrent validity [36].

Raw accelerometer data collected at 50 Hz will be processed into physical activity metrics using a machine-learned random forest classifier specifically designed and validated for assessing movement behaviours in free living adults [37]. The random forest classification model uses features in the raw acceleration signal to classify each 10-s window (epoch) as sedentary (lying or sitting still), stationary plus (active sitting, standing still, active standing), walking or running. Daily time spent in moderate-to-vigorous intensity physical activity (MVPA) will be calculated using the approach established by Ahmadi et al. in their analysis of accelerometer data from the UK biobank study [38]. Windows classified as walking with normalised gravitation units (milli g) ≥ 100 milli g and < 400 milli g will be considered moderate intensity physical activity (3–6 METs). Windows classified as walking with normalised gravitational units ≥ 400 milli g will be considered vigorous intensity physical activity (≥ 6 METs), while all windows classified as running will be considered vigorous intensity physical activity (≥ 6 METs). Non-wear periods will be identified and differentiated from sleep using the methods described by Ahmadi and colleagues [39]. The participants’ accelerometer data will be included in the analyses if they have ≥ 4 days (with at least 1 weekend day) in which daily wear time is ≥ 10 h [40]. Device-measured physical activity will be reported as the average minutes of MVPA per day or week for each time point and group.

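### The 10-hour valid-day rule is not limited to waking hours under round-the-clock wear, so a day with only about 1 to 4 recorded waking hours can count as valid for MVPA

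*Protocol article*

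**What the plan says.** All places are in the Protocol article.

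- **Wear schedule.** Primary outcome asks for wear "for 7 consecutive days during waking and sleeping hours, except when swimming, bathing or participating in contact sports". Procedure asks for it "for 7 consecutive days and nights from the day of receipt".
- **Non-wear.** "Non-wear periods will be identified and differentiated from sleep", by a cited method.
- **Valid day for the analysis.** Primary outcome needs at least 4 days, one of them at the weekend, "in which daily wear time is ≥ 10 h".
- **Valid day at entry.** Under Procedure, "Potential participants providing less than four valid monitoring days" are excluded, with the same 10 h of wear time defining a valid day.
- **Log.** Participants record removals, "time they went to bed and wake up time". No use of these times in the valid-day rule is stated.
- **Summary measure.** "Device-measured physical activity will be reported as the average minutes of MVPA per day or week for each time point and group".
- **Model.** Statistical analyses lists fixed effects for group, time and their interaction, plus a random subject effect. It names no wear-time term. Intention-to-treat is tied to having a valid baseline.

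**The concern.** A threshold of 10 h does different work depending on what it counts. Applied to waking wear, it ensures that most of the active day is observed. Applied to total wear on a monitor worn through the night, most of it can be met by sleep, when no MVPA occurs. The article distinguishes sleep from non-wear and then sets the threshold on daily wear time without restriction, so the plain reading is that worn sleep counts.

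A barely valid day then enters the mean as if fully observed, and MVPA in the unrecorded waking hours is in effect scored as zero. Multiple imputation does not help, because the day is not missing. The primary outcome would partly measure waking wear compliance as well as behaviour.

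**Working it through.** **1. The plan's own figure, for scale.** Sample size gives d = 0.45 for 10 min/day, 80% power, alpha 0.05 (two-sided assumed) and 76 per group.

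- n = 2 × (1.960 + 0.842)² / 0.45² = 77.5, so 78 per group (79 by the t-test). The stated 76 agrees to within 2 participants and gives about 79% power.
- Implied SD = 10 / 0.45 = 22.2 min/day.

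The sample size does not depend on the valid-day rule. It only provides a yardstick.

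**2. A day that just meets 10 h with the night fully worn.** Sleep length S is not in the documents and is assumed to be 6 to 9 h. Waking hours recorded = 10 − S. Share of the waking day recorded = (10 − S)/(24 − S). With MVPA spread evenly over waking hours (assumed), the share missed is one minus this.

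| S (h) | Waking hours recorded | Share recorded | MVPA missed | Share recorded if the 10 h were waking wear, 10/(24 − S) |
|---|---|---|---|---|
| 6 | 4 of 18 | 22% | 78% | 56% |
| 7 | 3 of 17 | 18% | 82% | 59% |
| 8 | 2 of 16 | 12.5% | 87.5% | 62.5% |
| 9 | 1 of 15 | 7% | 93% | 67% |

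**3. Effect on one participant's mean (S = 8 h, other days complete).** One such day among four valid days gives (3 + 0.125)/4 = 0.78, a fall of 22%. One among seven gives (6 + 0.125)/7 = 0.875, a fall of 12.5%.

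**4. Can it happen with good compliance?** This depends on how a day is delimited, which is not stated.

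- *Calendar days, last morning:* a device worn from midnight and removed at 10:00 has 10 h of wear. With waking at 07:00 (assumed), 3 of those hours are waking.
- *Calendar days, day of receipt:* 10 h before midnight needs a start by 14:00. With bedtime at 22:00 to 23:00 (assumed), that is 8 to 9 waking hours, so this day does not show the problem.
- *24-hour windows from receipt:* no truncated first day arises.

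**5. If such days are equally common in both arms.** Assume a fraction f of days sits at the threshold, S = 8 h, and SD stays at 22.2. The observed difference is 10 × (1 − f × 14/16).

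| f (assumed) | Observed difference (min/day) | Power at 76 per group |
|---|---|---|
| 0 | 10.0 | 79% |
| 5% | 9.6 | 76% |
| 10% | 9.1 | 72% |
| 25% | 7.8 | 58% |

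These values of f are illustrations. The documents give no wear data.

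**The case against.** **The article never says outright that sleep counts as wear.** Separating sleep from non-wear is also a step towards computing waking wear, bed and wake times are logged, and the cited methods may restrict wear to waking time. This stands as a limit: the reading is an inference. If a waking restriction is already in force, one sentence stating it settles the main point. It does not dispose of the concern, because the threshold is stated twice for round-the-clock wear and neither statement mentions waking hours. That is more than detail left to a fuller document.

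**The extreme day is a boundary case.** Apart from a truncated last day, it requires someone to wear the device all night and leave it off for most of the day, although removal is allowed only for a few activities. This also stands: nothing shows that such days are common.

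**The arms are measured alike.** Procedure gives both arms the same monitoring, reminders and vouchers, and change from baseline largely cancels stable personal wear habits. This is fair, but it does not cancel a change in wear between waves.

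**The remedy is partial.** With 8 h of sleep, a day with exactly 10 h of waking wear still misses 37.5% of MVPA. That is true, and it is why a wear-time sensitivity analysis belongs with the new rule.

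Three stronger readings are tempting and are not supported:

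- *The partial day of receipt qualifies in the same way.* Step 4 shows that it does not.
- *The group contrast is biased by a known amount.* For example, 30 min/day of MVPA and a 10-percentage-point imbalance in such days would give 30 × 0.10 × 14/16 = 2.6 min/day. Neither input is in the documents.
- *The Fitbit worn only by the intervention arm makes accelerometer wear differ between arms.* The article says nothing on this, and even its direction would be a guess.

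**Conclusion.** The concern holds as a mismatch between a stated rule and the stated wear schedule. On the plain reading, a day with about 1 to 4 recorded waking hours (9 to 6 h of sleep assumed) is valid for the primary outcome. About 93% to 78% of its expected MVPA is then missed if MVPA is spread evenly over waking hours. Nothing in the stated model or missing-data approach corrects this.

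The size of the effect on the trial result cannot be determined. Equal frequency in both arms shrinks the difference, and unequal frequency could bias it in either direction. The documents do not show that the comparison is materially biased. The rule should be corrected because a better one is available from data already collected.

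**What to change.** Before unblinding:

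1. Define a valid day for the outcome analysis as at least 10 h of **waking** wear, using the sleep detection or the bed and wake log, and apply it identically at baseline, 3 and 6 months. State how a day is delimited.
2. Exclude truncated first and last days that do not meet this rule.
3. Add a sensitivity analysis adjusting for mean waking wear time.
4. Keep every randomised participant in the intention-to-treat analysis. A baseline that fails the tightened rule is treated as missing, and the valid-baseline condition in Statistical analyses is amended to match. The entry check in Procedure has already been applied, since Trial status reports recruitment completed on 25 November 2024, and it need not be reopened.

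If the processing already uses waking wear, items 1 and 2 reduce to saying so in Procedure and Primary outcome.

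The cost is reprocessing of stored raw data. Some days or visits become invalid, which adds a little missing data to a trial that already allows for 30% dropout.
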